#### *Independent pain observer*

The staff in the experimental care homes will be aware of the pain treatment received by the participants. In view of the fact that possible expectancy bias may develop among staff in the experimental group as the study progress, the observational pain scale C-PAINAD will also be completed by an independent pain observer, who will be blinded to the study’s hypotheses, the allocation of participants to the experimental/control conditions, and their total pain treatment consumption. As mentioned, the pain assessment will be conducted weekly during the 16-week study period (baseline assessment for 4 weeks and Protocol implementation for 12 weeks) in both the control and experimental homes. Participants will perform the standardized exercise programme while the pain observer is assessing their pain. In previous studies, the standardized exercise programme successfully triggered pain-related behavioral responses [32,33]. The exercise programme will include a set of passive range of motion (ROM) exercises involving the movement of all major joints. Each ROM will be repeated 10 times or moved to the point of resistance and held for 10 seconds. The participants will then be asked to perform a set of active motions that include changing position from lying to sitting, from sitting to standing, and then from standing to walking. The design of this standardized exercise programme was based on a literature review and followed consultation with a physiotherapist and a nurse with long-term care experience. This exercise programme is similar to the daily stretching exercises performed by physiotherapists in care homes. It helps older people retain joint flexibility and avoid joint stiffness. It was specially designed and has been used to evaluate the psychometric properties of four observational pain scales, including PAINAD [34]. It is believed that if participants suffer from pain under routine nursing care activities, this exercise programme will generate a level of pain similar to that experienced by the participants. This exercise will be performed by another well-trained RA who will be blinded to the study hypothesis and group allocation.

#### *Control long-term care homes*

As in the experimental long-term care homes, four 1-hour workshops will be conducted by JL, addressing pain assessment and management for older people, during the first 4 weeks of the intervention cycle. The control care homes will continue their usual pain management strategies for the participants for the remaining 12 weeks of the intervention cycle. Similarly, participants’ weekly C-PAINAD scores will be collected by the independent pain observer throughout the 16-week study period. Their weekly MQS III score and weekly record of non-pharmacological pain treatments will be collected by another RA throughout the intervention cycle.

### Blinding

Two RAs, who will be blinded to the study hypothesis and group allocation, will be responsible for all subject assessment measures. One will be responsible for collecting MQS III scores and non-pharmacological pain treatment records. Another will work as the independent pain observer to collect participants’ observational pain scores. The pain observer will also be blinded to participants’ total pain medication consumption. We anticipate that after the training sessions, the staff in the care home will become more sensitive to residents’ behavioral patterns. To avoid a contamination effect caused by different time points in the Protocol implementation of different participants within the same care home, the pain management Protocol will be implemented for all participants in each care home simultaneously.

### Outcome measures

The effectiveness of the Protocol on pain management will be evaluated by: (1) the use of pharmacological pain treatments, measured by the Medication Quantification Scale III (MQS III); (2) the use of all non-pharmacological pain treatments recorded on the participants’ pain management record; and (3) pain-related behaviors exhibited by participants, which will be assessed by an observational pain scale (that is, C-PAINAD). The Protocol will be used to guide the pain management of the participants in the experimental condition for 12 weeks (that is, from the fifth to the sixteenth weeks of the intervention cycle). Intervention effects will be measured weekly and compared with the baseline measurements as well as between the experimental and control conditions to detect the progress of the effectiveness of the Protocol in pain management continually throughout the study period. Baseline measurements will be collected for 4 weeks (that is, between the first and fourth weeks of the intervention cycle).

#### *Medication quantification scale version III (MQS III)*

The MQS III will quantify the usage of pain medications [19,35]. The MQS I was used as an outcome indicator to demonstrate that regular use of an observational pain tool could significantly increase the total dosage of pain medications [13]. The MQS quantifies pain medications according to their daily administered dosage, pharmacological classification, and detriment weight (that is, the potential of each medication to produce side-effects) [19]. The concurrent validity of the MQS I was established by calculating the correlation coefficient (r = 0.755, *P* <0.01; two-tailed) between MQS I scores and the mean clinical judgment of pain management professionals [19]. The MQS III was updated in 2003 to modernize medication classifications and their detriment weights [36]. The MQS III has been validated and applied to the study of pain regimens in various pain conditions [37-39].

#### *Record of non-pharmacological pain treatments*

The common non-pharmacological interventions used for relieving pain among older people include, but are not limited to, heat and cold therapy, massage, transcutaneous electrical nerve stimulation (TENS), and acupuncture. Only interventions initiated by healthcare professionals will be recorded. The type and the total time per week of the treatments will be recorded during the study period. The non-pharmacological pain treatment will be recorded weekly for 4 weeks by the same RA, who is also responsible for collecting MQS III scores, according to participants’ nursing, physiotherapy or occupational therapy records prior to Protocol implementation (baseline period) and for the 12 weeks of Protocol implementation.

#### *Chinese - Pain Assessment IN Advanced Dementia (C-PAINAD)*

The C-PAINAD consists of five pain behaviors: breathing, negative vocalization, facial expressions, body language, and consolability. Each behavior is rated from 0 to 2 according to the severity of behavior exhibited, thus giving a total score of 0 to 10. Construct validity was supported by the C-PAINAD’s ability to differentiate pain from other pain-free conditions. It can detect pain among people with dementia. Exploratory factor analysis was used to evaluate the construct validity in which one major factor (that is, pain) was extracted and the percentage of variance was 51.2% [40]. The correlation coefficient was 0.68 when comparing the C-PAINAD with the Pain Visual Analog Scale. Generally, the findings were similar to those of the initial study validating the original PAINAD [28]. The results showed that the C-PAINAD was a simple, reliable, and effective pain assessment tool for cognitively impaired older people. A well-trained independent pain observer (that is, another research assistant who will not be involved in collecting data related to pain treatments) will use the C-PAINAD to observe participants’ pain scores weekly during the 4-week baseline assessment period. This will then continue weekly for 12 weeks during the Protocol implementation. Nurses in the experimental condition will also use the C-PAINAD to observe the pain-related behavior of participants daily for the 12 weeks of Protocol implementation. Pain scores collected by nurses will be compared to those collected by independent pain observers.

### Intervention fidelity and training of independent pain observer/research assistant

Across the intervention period, daily to weekly visits by research personnel will be arranged for each care home during the 12-week period. Particularly during the first 2 weeks of the Protocol implementation period, a member of the research team will visit the care homes daily to ensure the smooth implementation of the Protocol. If staff have difficulty following the Protocol, meetings will be arranged to answer their concerns.

An independent pain observer will be trained by JL on how to use the C-PAINAD. She will also practise pain assessment using the C-PAINAD with various clinical vignettes. On-site practice will also be arranged. An acceptable inter-rater reliability (ICC = 0.9) will be established by comparing the pain scores rated by the observers with those rated by JL, who is experienced in using the C-PAINAD. JL will also instruct and evaluate the use of all instruments by the RAs. Monthly quality control meetings will be arranged with all research personnel in this study. The inter-rater reliability between the pain observer and JL will be checked at least monthly throughout the entire study period.

### Statistical analysis and outcome measurement

Data will be analyzed using the Statistical Package for the Social Sciences (SPSS 19). Descriptive statistics will be generated for the demographic data. Normality assumptions for the variables will be checked. The paired t-test or Wilcoxon’s signed rank test will be used to examine any significant difference in the use of pain treatments and the change in the C-PAINAD score in the experimental group before and after implementation of the protocol. Student’s t-test or the Mann-Whitney U test will be used to examine any significant differences between the control and experimental groups in terms of the outcome variables. For categorical and dichotomous outcome variables, a χ2 test will be used to identify any significant differences between the groups. A *P* value ≤0.05 will be considered statistically significant. Mixed effect modelling (MEM) will be further used to take into account the intracluster correlation, to measure changes in the outcome measures after intervention with respect to its baseline, and to see the effectiveness of the intervention.

Multiple imputations will be adopted to manage all the missing data.

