The Protocol was used to guide the pain management of 30 care home residents with dementia, with at least one pain-related diagnosis, for 8 weeks. Before the implementation, only five residents had been prescribed pain medications. Pain medications administered to the residents were quantified by the Medication Quantification Scale (MQS) [19]. During the study period, the mean MQS score increased from 10 (SD 14.23) at week 1 to 23.41 (SD 10.58) at week 8. The percentage of residents given pain medications increased to 23.33% (n = 7) at week 8. Similarly, only six residents were receiving non-pharmacological interventions at week 1. Towards the end of the study period, 17 residents were receiving non-pharmacological pain-relieving interventions such as hot pads, ice therapy, and massage. The mean pain score of the 30 residents decreased slightly from 2.87 (SD 1.30) at week 1 to 2.57 (SD 1.32) at week 8. Although this study did not show a statistically significant reduction of pain scores, probably due to the small sample size, it did show clinical relevance in improving pain management. Incorporation of this Protocol into the long-term care home’s daily routine encouraged well-organized pain recording for each resident, allowing further comparisons of pain treatment effectiveness. Besides this pilot study, no other study has been conducted to evaluate the effectiveness of similar protocols in improving pain management practice.

The aim of this study is to investigate the extent to which the implementation of the Observational Pain Management Protocol can improve the management of pain for older care home residents with dementia. Based on the findings in our pilot study [18], we hypothesize that the implementation of the Protocol will result in an improvement in pain management for residents with dementia, as manifested in an increased use of both pharmacological and non-pharmacological pain treatments. As a consequence, behavioral pain scores will be lower due to better pain management. The following two research objectives have been derived:

1. To investigate whether a systematic use of the Protocol improves pain management, as manifested by the increased use of pharmacological and non-pharmacological pain treatments for residents with dementia.

2. To investigate whether the use of this Protocol results in lower observational pain scores for residents with dementia.

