#### *Sample size*

We will randomly select eight long-term care homes that agree to join this study. As no similar cluster-randomized trial has been reported in the literature, we can only estimate the intracluster coefficient with a range between 0 and 0.1 [22]. The intensity of pain can vary according to the different natures and sources of the pain. As this study is not limited to participants suffering from a particular type of pain, we anticipate that variations in the nature of participants’ pain will be considerable. Due to its heterogeneous nature, we assumed an intracluster correlation of 0.02. The pilot study was able to detect a mean difference of 13.41 points on the MSQ score (95% confidence interval 8.923 to 17.897) and -0.3 points on the C-PAINAD (95% confidence interval -4.459 to 0.169) between the pre- and post-tests [18]. After averaging the effect sizes calculated based on these two mean differences, this was equivalent to an effect size of 0.65. In order to secure an appropriate effect size, a more conservative approach of using an effect size of 0.4 was used to calculate the sample size. With a significance level (α) of 0.05 and power (1-β) 0.8 for a two-sided test, the sample size calculation gives about 38 participants for each group in order to evaluate a mean difference in MSQ and C-PAINAD scores between the experimental and control groups. Accounting for the intracluster correlation, a variance inflation factor of 1.31 will be multiplied to this calculated sample size. Further accounting for a 15% drop-out rate over the period based on two similar studies [13,18], a total number of 61 participants per group is required, resulting in a total proposed sample size of 122. This means we will recruit 15 to 16 participants in each long-term care home.

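### For MQS III, a normality check can move the treatment comparison from means to ranks, and the plan does not say whether that test or the mixed model decides

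*Protocol article*

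**What the plan says.** All references are to the protocol article.

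- **Statistical analysis and outcome measurement.** The section opens its inferential part with "Normality assumptions for the variables will be checked". No test or threshold is named.
- It then gives pairs of tests. Within the experimental group: "The paired t-test or Wilcoxon’s signed rank test will be used to examine any significant difference in the use of pain treatments". Between groups: "Student’s t-test or the Mann-Whitney U test will be used to examine any significant differences between the control and experimental groups". The normality check is the only thing offered that could select within each pair. The link is implied, not written out.
- After the significance threshold, the same section adds: "Mixed effect modelling (MEM) will be further used to take into account the intracluster correlation, to measure changes in the outcome measures". It does not rank this model against the simple tests.
- **Sample size.** The calculation is made "in order to evaluate a mean difference in MSQ and C-PAINAD scores between the experimental and control groups" (MSQ is the article's misprint for MQS).
- **Background.** On the pilot: "The percentage of residents given pain medications increased to 23.33% (n = 7) at week 8". Before implementation, five of the 30 residents had a prescription.

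**The concern.** A t-test and a Mann-Whitney test on MQS III do not ask the same question. The first compares the average amount of medication over all residents. The second compares the ranks of the two groups, and when most scores are tied at zero the ranks mostly record whether a resident has any analgesic at all. The first objective, increased use of treatment, could be met by more users, by more medication per user, or by both.

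The plan lets a preliminary check on the shape of the data settle which of these questions is tested. With many zeros the answer to that check is known before the trial starts. The mixed model, which works on means, may then disagree with the rank test, and the plan has no rule for that case. The stake is an MQS III conclusion that depends on which of two pre-announced analyses is put forward.

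**Working it through.** **1. What the trial was sized on.** The standard formula for comparing two means, two-sided 5% and 80% power, is n = 2(1.96 + 0.84)² / d². With d = 0.65 it gives 38 per group, the printed figure. With the stated d = 0.4 it gives 99. That mismatch is a separate matter. Here it matters only that the sizing is for a difference in means. Retained residents per arm: 61 × 0.85 = 51.85, taken as 52.

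**2. How many MQS scores are zero.** From the pilot: 25/30 = 83% at the start (assuming those prescribed analgesics are the users at week 1) and 23/30 = 77% at week 8.

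**3. Whom the printed MQS means describe.** The article prints 10 (SD 14.23) at week 1 and 23.41 (SD 10.58) at week 8. If all 30 residents were averaged, with k users and the rest zero, the SD would have to be at least mean × √((30 − k)/k) × √(30/29):
- week 1: 10 × √(25/5) × √(30/29) = 22.7, against 14.23 printed;
- week 8: 23.41 × √(23/7) × √(30/29) = 43.2, against 10.58 printed.

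So the printed figures cannot describe all 30 with these user counts. I take them as users-only, which is an assumption. The all-resident means are then 10 × 5/30 = 1.7 and 23.41 × 7/30 = 5.5.

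**4. Does the check fail?** In simulated MQS data (zero for non-users, gamma among users), Shapiro-Wilk rejects in 100% of runs at user shares of 17-50%. Shapiro-Wilk is my choice of check, since the article names none.

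**5. What Mann-Whitney then measures.** Compare one control resident (user probability 5/30) with one experimental resident (7/30):
- both zero: 25 × 23 / 900 = 63.9% of pairs, all ties;
- only the experimental resident is a user: 7 × 25 / 900 = 19.4%;
- only the control resident is a user: 5 × 23 / 900 = 12.8%;
- both are users: 5 × 7 / 900 = 3.9%.

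Dose matters only in the last 3.9%. The Mann-Whitney quantity is 0.194 + 0.639/2 + 0.039q, where q is the chance that the experimental user has the higher score. With no dose effect (q = 0.5) it is 0.533. With the largest possible dose effect (q = 1) it is 0.553.

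**6. Power for MQS, two-sided 5%, 52 per arm, no clustering.**

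| Scenario | Mean comparison | Mann-Whitney |
|---|---|---|
| Pilot-like: 17% to 23% users and higher dose | 57% (61% in a second simulation) | 21% (22%) |
| Same, home-level summaries on 6 df | 44% | 17% |
| Dose only, low user share | 42% | 7% |
| Dose only, 50% users | 76-84% | 36-39% |
| Dose only, 80% users | 96-99% | 98% |
| Uptake only, 17% to 40% | 44-52% | 74-76% |

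For the dose-only change at 17-23% users and 52 or 61 per arm, the full range is 30-47% against 5-8%.

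**7. C-PAINAD.** Modelled as a rounded normal score with the pilot mean 2.87 and SD 1.30, a single week is rejected in 99-100% of runs. A 12-week mean is rejected in only 4-9%. For a shift of 0.4 × 1.30 = 0.52 points, power at 52 or 61 per arm is 50-56% for the t-test and 48-54% for Mann-Whitney.

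**The case against.** The strongest reply is that the same section plans a mixed model, which estimates change in means and allows for clustering. A reader might infer from the list of tests that the trial ends on rank tests. The text does not support that: the rank test is one of two announced analyses. What remains is that the model is introduced as an addition and nothing makes it decisive.

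Second, the selection rule is implied, and no formal normality test is named. A plot or a skewness check might let a rounded C-PAINAD score pass. This stands for C-PAINAD. It helps little for MQS III with about 80% zeros, which would look non-normal by any method.

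Third, a reader might extend the criticism to C-PAINAD. The article does not say that single-week scores are tested, averages over the implementation period usually pass, and the two tests have nearly the same power. No consequence is shown.

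Fourth, the MQS III loss depends on the scenario. The trial's user share is unknown, and more users is also increased use, so the rank test does not answer an irrelevant question. It is the better test when only uptake rises. All of this stands. It limits the size of the point, but it also shows that the choice of test is a choice of question, to be made in advance.

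Finally, an unseen analysis plan may settle the hierarchy. The point concerns what the article itself states.

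**Conclusion.** The point holds for MQS III, in a limited form. The article lets a normality check choose between a mean and a rank comparison and leaves open whether that test or the mixed model decides. If users are as few as in the pilot, the check fails almost surely and the rank test has about 21% power where the mean comparison has about 57%, or 7% against 42% if only the dose changes.

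These figures rest on users-only pilot means, gamma doses, pilot user shares based on 5 and 7 people, 52 per arm and no clustering. They do not show that rank tests are generally worse for this outcome, and no inflation of type I error from the switch has been shown. This is worth correcting before the data are seen, but it does not invalidate the trial.

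**What to change.** Remove the normality-driven choice, with its Wilcoxon and Mann-Whitney alternatives, as the test of effect. State that:

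- for MQS III and C-PAINAD the effect is the between-group difference in means over all residents, with MQS III set to zero when no analgesic is given;
- it is estimated from the planned mixed model with home as a random effect, and this analysis is decisive;
- the share of residents with any analgesic is a separate named result, also analysed with allowance for clustering.

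Putting a plain t-test in place of the rank test would not be enough, because it ignores clustering. In simulation with 15 residents per home, its type I error for C-PAINAD was about 7.6% at an intracluster correlation of 0.02 and 20% at 0.1.

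A permutation of homes can support the model but should not be a second decision rule. With four homes per arm (assumed) there are 8!/(4! × 4!) = 70 allocations, so the smallest two-sided p is 2/70 = 0.029 and the next is 4/70 = 0.057.

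The cost is wording and a few lines of analysis. The downside is lower power than a rank test if the intervention raises only the number of users. The separate user-share result covers that case.

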## Methods/design

### Study design

A two-group, single-blinded, cluster-randomized controlled trial (RCT) will be used to examine the effect of the Protocol on pain management for older people with dementia as compared to a control condition of usual pain management practice in long-term care homes. This study will take 16 weeks (that is, baseline assessment and care home staff training for 4 weeks and Protocol implementation for 12 weeks). Participants in the control condition will continue usual pain management practice according to their care homes. Intervention effects will be measured weekly and compared with the weekly baseline measurements for 4 weeks, as well as between the experimental and control conditions, to detect the progress of the effectiveness of the Protocol in pain management continually throughout the study period. The overall study design is illustrated in Figure 1.

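### The before/after test in the experimental arm alone is not ranked below the between-arm tests, so a change shared with the control homes could be reported as a Protocol effect

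*Protocol article*

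**What the plan says.** Under Statistical analysis and outcome measurement, the first inferential step is: "The paired t-test or Wilcoxon’s signed rank test will be used to examine any significant difference in the use of pain treatments", together with C-PAINAD change, "in the experimental group before and after implementation of the protocol". No matching test is given for the control group. The between-arm step follows: "Student’s t-test or the Mann-Whitney U test will be used to examine any significant differences between the control and experimental groups" on the outcome variables, with χ2 tests for categorical outcomes. One threshold is then set: a P "value ≤0.05 will be considered statistically significant". Last, "Mixed effect modelling (MEM) will be further used to take into account the intracluster correlation", to measure change from baseline and to judge whether the intervention works. No test is named as primary, and none is described as descriptive or supportive.

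The Outcome measures section defines what counts as an effect: "Intervention effects will be measured weekly and compared with the baseline measurements as well as between the experimental and control conditions". The Study design section says much the same and gives the purpose as "to detect the progress of the effectiveness of the Protocol in pain management continually throughout the study period". Both sections place the comparison with baseline beside the randomised comparison, as two ways of measuring an intervention effect.

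On the control homes, the protocol says: "As in the experimental long-term care homes, four 1-hour workshops will be conducted by JL, addressing pain assessment and management for older people". Both arms also have the independent observer's weekly C-PAINAD assessment during the standardised exercise for 16 weeks.

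**The concern.** A paired test within one arm asks whether that arm changed. It does not ask whether the Protocol changed it. Anything that moves both arms counts towards significance, and this design has several candidates: pain workshops in both sets of homes, 16 weekly observed sessions, and residents growing used to the exercise that is meant to provoke the pain behaviour. The control homes were included to remove such influences, and this test does not use them. It repeats the uncontrolled pre/post comparison of the pilot, although the Discussion says a randomised trial is needed to obtain stronger evidence.

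The test also treats residents of the same home as independent. That is a second weakness, and curing it would not cure the first: a cluster-adjusted before/after test would still have no comparator.

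The risk is in the reporting. With one significance rule and no ranking, a significant before/after result beside a null between-arm result could be presented as improved pain management.

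**Working it through.** **Is there a figure in the plan to reproduce?** No. The plan gives no error rate for this test and no SD of change. The figures below are an illustration of scale.

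**Inputs**
- Pilot C-PAINAD change -0.3, printed 95% interval -4.459 to 0.169 (Sample size); 30 residents (Background).
- 61 residents per arm and 15% drop-out (Sample size): 61 × 0.85 = 51.85, taken as 52 completers.
- Four homes per arm, assuming the eight homes split equally: 52 / 4 = 13 completers per home.
- Two-sided test, P≤0.05.
- Intracluster correlation 0.02 assumed, range 0 to 0.1 (Sample size). That these values apply to change scores is an assumption.
- Size of a shared shift: not in the protocol. Assumed 0.2 to 0.5 points.

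**SD of change.** From the upper limit, the half-width is 0.169 - (-0.3) = 0.469. With t(0.975, 29) = 2.045, SD = 0.469 / 2.045 × √30 = 1.256. The printed interval is not symmetric about -0.3: its midpoint is (-4.459 + 0.169) / 2 = -2.145, and the lower limit by the same formula gives 4.159 / 2.045 × √30 = 11.1. That is not credible beside the pilot's cross-sectional SDs of 1.30 and 1.32. The value 1.26 is therefore a plausible assumption, not a figure the protocol establishes.

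**Rejection probability of the paired t-test with no Protocol effect.** Noncentrality = shift / SD × √52, 51 degrees of freedom, critical value 2.008.

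| Shared shift (points) | Noncentrality (SD 1.256) | P(paired test significant) |
|---|---|---|
| 0.2 | 1.15 | 20% |
| 0.3 | 1.72 | 39% |
| 0.4 | 2.30 | 62% |
| 0.5 | 2.87 | 80% |

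Sensitivity to the SD at a 0.3 shift: SD 1.0 gives noncentrality 2.16 and 56%; SD 2.0 gives 1.08 and 19%.

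**Comparison with a randomised contrast.** In simulation (four homes of 13 per arm, same shift in both arms), a t-test on home mean changes between arms is significant in about 5% of trials at every shift and at intracluster correlations of 0, 0.02 and 0.1.

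**Clustering.** With no shift at all, the paired test is significant in about 8% of trials at a correlation of 0.02 and about 19% at 0.1. With a shift, clustering does not always raise the figures:

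| Correlation | 0.2 | 0.3 | 0.4 | 0.5 |
|---|---|---|---|---|
| 0 | 20% | 40% | 62% | 80% |
| 0.02 | 23% | 40–41% | 61% | 78% |
| 0.1 | 31% | 44% | 59% | 73% |

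Extra variance in the mean raises rejection when it is below about one half and lowers it when it is above.

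**The case against.** The strongest reply is that the paired test does not decide anything. The protocol says only that it will examine differences, and the aim of judging effectiveness is attached to the mixed model. The Study design section frames the effect against usual practice, the sample size is built on a difference between groups, and each passage that mentions comparison with baseline also mentions comparison between conditions. Ranking and labelling are also matters that an analysis plan commonly settles.

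Much of this stands. A reader might infer that a shared change would be declared an effect, or that the plan discards the randomisation. The text supports neither: a shared change could be declared an effect if the paired result is read as evidence, and only this one test leaves the randomisation unused. What does not fall away is that the test is stated, under the common threshold and in one arm only, and that comparison with baseline is called an intervention effect. That is stated text, not an omission left to another document.

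Three further cautions are fair:
- Regression to the mean is a tempting extra mechanism, but eligibility sets no C-PAINAD or MQS threshold, so it is weakly supported and is not relied on here.
- The workshops and four weekly baseline assessments fall in weeks 1 to 4, so part of any training or habituation effect is already inside baseline.
- A 0.3-point fall was seen in the pilot while the Protocol was in use. Treating that amount as unrelated to the Protocol is hypothetical.

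**Conclusion.** The point holds in a limited form. The plan includes an experimental-arm-only significance test with no comparator and no allowance for clustering, and does not place it below the between-arm tests. A change shared with the control homes could therefore be reported as a Protocol effect.

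The size depends on two assumptions: an SD of change taken from one limit of an asymmetric interval, and a shared shift the protocol does not quantify. Across the SDs and shifts examined, the paired test is significant in about 19% to 80% of trials with no Protocol effect, against about 5% for a home-level contrast between arms. The qualitative conclusion needs neither assumption, because the test cannot separate a shared change from an effect of the Protocol whatever the SD. It would be wrong to add that home-level correlation always makes these figures worse; the larger ones fall slightly.

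This should be corrected, but the plan already contains the analysis that answers the question.

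**What to change.** - Remove the paired t-test and Wilcoxon test as tests of effect.
- Report change from baseline descriptively, with confidence intervals, for both arms.
- State that the effectiveness conclusion rests only on the between-arm contrast of change in the mixed model already planned: group by period, adjusted for baseline, with home as a random effect and a correction suited to only eight homes.
- In the Study design and Outcome measures sections, describe comparison with baseline as showing the course within each arm, and keep the term intervention effect for the comparison between arms.

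The cost is a few sentences, with no extra data, staff or participants. The Trial status section says homes are still being recruited, so at that stage the change can be made before any outcome is seen.
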